### Follow-up

Participants will be followed on the same service. Between 40 and 60 days postpartum, they should return for postpartum consultation and pelvic ultrasound to assess the IUD and cut the wires (see Table 1). In cases where the woman has an IUD in situ and without visualization of the threads in the cervical canal, the follow-up will be exclusive with pelvic ultrasound. For women who have expelled IUDs or who have IUDs in the cervical canal, a new device of the woman’s preference will be offered. In cases where the woman is not satisfied with IUD, another contraceptive method will be offered and made available.

**Table 1 Tab1:** Procedures and techniques

	Study period					
	Enrollment		Allocation	Post allocation		
	Prenatal consultations	Admission for childbirth	Randomization	Immediately after randomization	In the labor and delivery room following delivery	Postpartum consultations and pelvic ultrasound
**Timepoint**	**T−2**	**T−1**	**T0**	**T1**	**T2**	**T3**
**Enrolment:**						
**Preinclusion**	x					
**Eligible patients**		x				
**Signing of the consent form**		x				
**Allocation**			x			
**Interventions:**						
**Manual insertion**				x		
**Forceps insertion**				x		
**Assessments:**						
**Pain or discomfort during insertion**					x	
**Expulsion**						x
**Uterine perforation**						x
**Proper positioning**						x

Orientation, insertion, and removal of misplaced IUDs will be performed by a group of trained resident physicians and supervised by an experienced chief. To guarantee the standardization and constant review of the technique, periodic training offered by the researchers is planned. After insertion, the professional responsible for the procedure is recorded so that we can later correlate whether the expulsion and/or mispositioning was influenced by the experience of the professional who performed the procedure.

The insertion technique will be briefly described below. For insertion with the forceps, the patient must be in a lithotomy position with the feet or knees supported. Asepsis of the vulva, vagina, and cervix will be performed with aqueous chlorhexidine solution. The uterus will be palpated to assess the fundus and tone. The evaluator must wear sterile gloves and must gently insert the vaginal speculum. The anterior labrum of the cervix should be clamped with a Collin clamp. The physician’s nondominant hand rested on the uterine fundus. The IUD should be secured using modified Kelly forceps (see Fig. 1). The physician's nondominant hand rested on the uterine fundus, and the IUD was gently placed through the cervix using forceps. The forceps must then be opened and withdrawn completely from the side. The clamp from the labrum of the cervix and the vaginal speculum should both then be removed.

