### Sample size

To calculate the sample size, the proportion between 2 groups method for comparison was used, setting the level of significance alpha or type I error at 5% (alpha=0.05) (or 95% confidence interval) and the power of the sample at 80% (or 20% type II error (beta=0.20)), according to Hulley et al. (2007) [14], and using the expulsion ratio values after IUD insertion in vaginal delivery in each group, obtained from a literature article [15]. Based on the results, it was estimated that a sample of *n*=186 women (*n*=93 with manual insertion and *n*=93 with forceps) would be representative for comparison of expulsion between the 2 groups.

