### Statistical analysis

The collected data will be coded and stored anonymously in a database created with Excel for Windows software for this purpose. Data will be allocated in tables and graphs for descriptive statistical analysis (mean, standard deviation, absolute and relative frequency distribution). The crossings involving a qualitative variable and a quantitative variable will be performed using parametric and nonparametric comparison tests, according to the distribution of data. The crossings involving two quantitative variables will be performed by calculating correlation coefficients and the crossings between two qualitative variables using association tests. Open questions will be categorized for application of statistical analysis. Continuity and discontinuation rates and their reasons will be evaluated by life table according to Kaplan–Meier. The significance level adopted for the statistical tests will be 5%. For statistical analysis, the Statistical Analysis System (SAS), version 9.4, will be used. All material used for data collection will be stored by the researcher for five years, remaining confidential. The results of the study will be published in an indexed scientific journal. This article has followed the SPIRIT guidelines for its elaboration [16].

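### The tests named for the operator-experience question ignore that women share an operator; with an assumed 10 to 20 operators and ICC of 0.05 to 0.10, the false-positive rate would be about 10% to 24% instead of 5%

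*Protocol article*

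**What the plan says.** In the Follow-up section, after Table 1, the article states that insertions are "performed by a group of trained resident physicians and supervised by an experienced chief". It continues: "After insertion, the professional responsible for the procedure is recorded", and the reason given is that "we can later correlate whether the expulsion and/or mispositioning was influenced by the experience of the professional who performed the procedure".

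The Statistical analysis section sorts the planned analyses by type of variable. A qualitative against a quantitative variable gets a parametric or nonparametric comparison test. Two quantitative variables get a correlation coefficient. The third case is "the crossings between two qualitative variables using association tests". The only other method is Kaplan–Meier for continuation and discontinuation. One level covers everything: "The significance level adopted for the statistical tests will be 5" per cent.

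No operator term, random effect, GEE or cluster-robust error is named. The article does not give the number of operators, their caseloads, an ICC or a definition of experience. It also does not say outright that women will be treated as independent.

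**The concern.** Women are randomised and measured, but experience is a property of the person inserting the device. Several women treated by one resident carry the same or a similar experience value, and they also share whatever else distinguishes that resident. Expulsion against experience must fall into one of the named kinds of test, however experience is coded, and in standard form each assumes independent observations. The variance is then understated whenever operators differ for reasons other than experience.

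The analysis uses the primary outcome (expulsion) and a listed secondary outcome (positioning), and asking whether experience had an influence is an inferential question. One or two residents with unusually high or low expulsion could produce a significant experience effect that is only variation between operators.

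**Working it through.** **Inputs from the article.** 186 women, 93 per arm (Sample size); significance level 5% (Statistical analysis; sidedness is not stated, two-sided assumed); a group of trained residents as inserters (Follow-up).

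**Inputs assumed.** Number of operators K from 6 to 40; ICC from 0.01 to 0.10; experience fixed per operator; equal caseloads unless stated.

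**The plan's own figures.** The 93 per arm can be neither reproduced nor refuted, because the article cites its expulsion proportions without giving them. Many pairs lead to 93 at 80% power: 17% v 35% or 30% v 50% without continuity correction, 10% v 27% with it. Nothing below depends on the pair. The nominal 5% does reproduce when women are independent: exactly 5.0% by formula, and 5.0% to 5.3% by simulation at ICC 0 with equal caseloads.

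**Formula.** For an exposure fixed per operator, with m = 186/K women per operator:

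- design effect DE = 1 + (m − 1) × ICC
- actual two-sided error = 2 × [1 − Φ(1.96/√DE)]

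**Examples.**

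- K = 10, ICC 0.05: m = 18.6; DE = 1 + 17.6 × 0.05 = 1.88; 1.96/√1.88 = 1.43; error 15.3%.
- K = 10, ICC 0.10: DE = 1 + 17.6 × 0.10 = 2.76; 1.96/√2.76 = 1.18; error 23.8%.
- K = 20, ICC 0.05: m = 9.3; DE = 1 + 8.3 × 0.05 = 1.42; 1.96/√1.42 = 1.65; error 9.9%.

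| Operators | ICC 0.01 | ICC 0.02 | ICC 0.05 | ICC 0.10 |
|---|---|---|---|---|
| 6 | 8.6% | 12.1% | 21.5% | 32.7% |
| 10 | 7.1% | 9.2% | 15.3% | 23.8% |
| 15 | 6.3% | 7.7% | 11.8% | 18.0% |
| 20 | 6.0% | 7.0% | 9.9% | 14.7% |
| 30 | 5.6% | 6.2% | 8.1% | 11.2% |
| 40 | 5.4% | 5.8% | 7.1% | 9.3% |

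**Simulation check.** Beta-binomial data were simulated 20,000 times per setting, with half the operators labelled experienced, no true effect, expulsion of 10% or 20%, and 6, 10, 20 or 30 operators. The results agree with the formula within about 1.5 points and hardly depend on the expulsion rate. Unequal caseloads (4,000 runs, expulsion 15%) raise the error: 18.6% and 29.0% with 10 operators at ICC 0.05 and 0.10, and 13.4% and 20.8% with 20 operators.

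**What doubling or quadrupling needs.** An error of 10% needs DE = (1.96/1.645)² = 1.42, that is, an ICC of 0.024, 0.051 or 0.081 with 10, 20 or 30 operators. An error of 20% needs DE = (1.96/1.282)² = 2.34, that is, an ICC of 0.076, 0.161 or 0.257.

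**After the fix.** A t test on operator-level proportions, simulated with equal caseloads, 6 to 30 operators and ICC 0 to 0.15, rejects in about 3.7% to 5.2% of null trials.

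**Randomised comparison.** With 12 operators each inserting in both arms, the simulated type I error is 4.9% at ICC 0 and 5.2% at ICC 0.05. Power for an assumed 10% v 26% is 82.6% and 82.0%.

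**The case against.** The strongest reply is that a journal article condenses the protocol, and that adjusting an ancillary question for clustering is normally left to the analysis plan. The Follow-up text gives a reason for collecting a variable and names no test, and the Statistical analysis section never links a test to it. Operator experience is not among the aims, the listed outcomes or the basis of the sample size. Supervision and periodic training are meant to keep operators alike, so the ICC may be small.

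Much of this stands. A fuller plan could resolve the point, the question is ancillary, and the size rests on assumptions. It does not remove the point. The article is not silent on method: it assigns every crossing of two variables to a class of test, and none of those classes fits an exposure shared by several women.

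A reader might go further in three ways that the article does not support:

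- **That false positives occur two to four times too often.** This describes only part of the assumed grid. The multiplier runs from about 1.1 (5.4/5) to 6.5 (32.7/5). With 30 or more operators, or an ICC of 0.02 or less, it is mostly below two. If experience is counted at each insertion it varies within operator, and the inflation is smaller than the table shows.
- **That the effective sample is the number of operators.** This would need an ICC of 1. With 10 operators and ICC 0.05 it is 186/1.88, about 99 women.
- **That the comparison of manual with forceps insertion is compromised.** Nothing in the article ties an operator to one technique, and the simulation shows no material effect when operators work in both arms.

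**Conclusion.** The point holds as a limited one. The named tests do not account for operator clustering. Applied to women as written, they exceed 5% whenever operators differ for reasons other than experience. With an assumed 10 to 20 operators, ICC of 0.05 to 0.10, equal caseloads and experience fixed per operator, the false-positive rate is about 10% to 24%. Across 6 to 40 operators and ICC of 0.01 to 0.10 it lies between about 5.4% and 33%; at ICC 0 the test is valid. Neither the number of operators nor the ICC is in the article, so no single figure can be given for this trial. The main randomised result stands, and this is a worthwhile improvement, not a flaw in the design.

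**What to change.** In the Statistical analysis section, take the experience question out of the generic tests. Define the experience measure in advance, for example the operator's number of prior insertions at that date. Analyse expulsion and mispositioning with a logistic model that has a random intercept for the recorded operator, or with GEE clustered on operator and a small-sample correction. Include arm and experience as covariates. If operators are few and experience is fixed per operator, compare operator-level proportions or use a permutation test at operator level; these do not suit a measure that changes within operator. Label the result exploratory.

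This costs a few sentences, because the operator is already recorded and the stated software, SAS 9.4, fits these models. The downside is a wider interval and lower apparent power for this ancillary question.

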**Fig. 1 Fig1:**
[figure not shown]
Modified Kelly forceps

For manual insertion, the patient must be in a lithotomy position with the feet or knees supported. Asepsis of the vulva, vagina, and cervix will be performed with an aqueous chlorhexidine solution. The uterus will be palpated to assess the fundus and tone. The evaluator must wear sterile gloves and must gently insert the device by holding it between the second and third fingers of the hand. The hand must be closed in order to completely protect the IUD so that it does not touch the vaginal walls (see Fig. 2). The physician’s nondominant hand rested on the uterine fundus, and the IUD was gently placed through the cervix and into the fundus.

**Fig. 2 Fig2:**
[figure not shown]
Hand position for IUD protection during insertion

In the puerperal review appointment, carried out between 40 and 60 days by a multidisciplinary team (physician, nurse, and psychologist), a pelvic physical examination will be performed and a questionnaire will be applied to assess, among other questions, the breastfeeding pattern (exclusive, mixed or artificial), bleeding pattern, signs of infection, pelvic pain, return to sexual activity, degree of patient satisfaction with the method, in addition to the desire to continue using the IUD or switch to other methods. When the patient is not sure whether she wants to continue with the IUD or has a transient complaint that can be clinically managed, such as increased bleeding, a new appointment will be scheduled between 30 and 60 days.

Transvaginal ultrasound will be performed at the Hospital’s Diagnostic Imaging Department to assess the proper positioning of the IUD using the Voluson 730 Expert Device, transvaginal, endocavitary probe, transvaginal preset, frequency of 6.5 MHz, mode B, with adjusted focus, gain, and depth. For normal-positioned IUDs and with satisfied patients, the wires will be cut when apparent. For badly positioned IUDs inside the uterine cavity or for those in the endocervical canal, the device will be removed, and a new device will be inserted if the patient desires. In the case of a mispositioned IUD without visible threads, removal will be performed with Hartmann forceps, when possible, or by hysteroscopy. In case of IUD expulsion, the patient will also be offered a new IUD. In the case of uterine perforation, abdominal radiography or a computed tomography scan will be performed to identify the device in the abdominal cavity. The removal will be done by laparoscopy*.* In the case of infection, the patient will be promptly treated with antibiotic therapy and the IUD will be removed if necessary*.* The data referring to the insertions will be analyzed quarterly and presented in the meeting of professors of the obstetrics department of the State University of Campinas to evaluate the feasibility of maintaining the study. In case of the need to modify the protocol of this study after evaluation by obstetrics professors, it will be communicated to the Research Ethics Committee for consideration. Participants will also be communicated at the puerperal review appointment.

Participants who have complaints related to the intrauterine device and have already attended the postpartum consultation may seek the hospital’s emergency care unit for gynecological evaluation. As many women remain in amenorrhea during lactation, when menstrual cycles return and in case of increased flow or the presence of cramps that bring discomfort, they should also return for a new gynecological evaluation.

### Sample size

To calculate the sample size, the proportion between 2 groups method for comparison was used, setting the level of significance alpha or type I error at 5% (alpha=0.05) (or 95% confidence interval) and the power of the sample at 80% (or 20% type II error (beta=0.20)), according to Hulley et al. (2007) [14], and using the expulsion ratio values after IUD insertion in vaginal delivery in each group, obtained from a literature article [15]. Based on the results, it was estimated that a sample of *n*=186 women (*n*=93 with manual insertion and *n*=93 with forceps) would be representative for comparison of expulsion between the 2 groups.

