**Methods:**

Randomized, controlled, open clinical trial. The study group will be composed of women between 18 and 43 years old who are admitted for vaginal birth at the Women’s Hospital of the State University of Campinas and who wish to use the IUD as a contraceptive method. The sample will be randomized into two insertion groups: manual and forceps. To calculate the sample size, the method of comparing the proportion between 2 groups was used, setting the level of significance alpha at 5% (alpha=0.05) and the power of the sample at 80% (beta=0.20). Based on the results, it was estimated that a sample of *n*=186 women (*n*=93 with manual insertion and *n*=93 with forceps) would be representative for comparison of expulsion between the 2 groups. All participants will undergo a postpartum consultation 40–60 days after birth with transvaginal ultrasound to assess the proper placement of the IUD.

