### Inclusion and exclusion criteria

The study will include women between 18 and 43 years old, with a single pregnancy, who have vaginal birth, who wish to use the IUD as a contraceptive method, and who do not have contraindications, namely, uterine malformation; uterine fibroids that deform the cavity; diagnosis or suspicion of ovular infection; diagnosis or suspicion of infection elsewhere; active sexually transmitted infection; and severe anemia (hemoglobin less than 8.0 mg/dl during antenatal care). Women who, after signing the consent form and randomization, wish to withdraw from the study for any reason, present with fever during labor or delivery, rupture of amniotic membranes for more than 24 h, manual extraction of the placenta, postpartum hemorrhage or uterine atony will be withdrawn from the study.

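### The stated 80% power for 186 women carries no allowance for withdrawal after randomisation or for loss before the 40–60 day visit, so it is not assured for the women analysed

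*Protocol article*

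**What the plan says.** The Sample size section fixes the type II error first of interest here: "the power of the sample at 80% (or 20% type II error (beta=0.20". Its type I error is worded this way: "setting the level of significance alpha or type I error at 5% (alpha=0.05) (or 95% confidence interval". The effect size comes from outside: "using the expulsion ratio values after IUD insertion in vaginal delivery in each group, obtained from a literature article [15". From these inputs alone it concludes that 186 women, 93 per insertion method, "would be representative for comparison of expulsion between the 2 groups". The Abstract repeats the inputs, "setting the level of significance alpha at 5% (alpha=0.05) and the power of the sample at 80% (beta=0.20", and says that the sample is to be randomised into the two groups.

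The section on inclusion and exclusion criteria then removes women who have already consented and been randomised. It gives six reasons: the woman's own wish, fever in labour or delivery, membranes ruptured for more than 24 hours, and the three that close the list, "manual extraction of the placenta, postpartum hemorrhage or uterine atony will be withdrawn from the study". It does not say that they are replaced, and neither does any other section.

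The primary outcome is the expulsion rate. Table 1 places its assessment at the postpartum consultation only, and the Follow-up section describes that visit: "Between 40 and 60 days postpartum, they should return for postpartum consultation and pelvic ultrasound to assess the IUD". No section gives an expected rate of withdrawal or non-return.

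**The concern.** A sample size computed from alpha, power and two proportions is the number of women who must contribute an outcome. Here it is presented as the number to be randomised, while the same article provides for removing randomised women and reads the outcome weeks after discharge. If some of the 186 have no expulsion result, the comparison is made on fewer than 93 per arm, and the power for the planned difference is lower than the figure printed in both the Abstract and the Sample size section.

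What is at stake is the accuracy of the one power statement the trial relies on for its primary outcome. The validity of the comparison is not in question here.

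**Working it through.** **Inputs from the article.** Alpha 5%, power 80%, 93 per arm with 1:1 allocation, binary outcome (expulsion). Sidedness is not stated. I take two-sided, because the Sample size section pairs alpha with a 95% confidence interval and the Statistical analysis section says only "The significance level adopted for the statistical tests will be 5".

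**Inputs not in the article.** The two expulsion proportions, the formula variant and the loss rate *d*. The loss rate is my assumption, shown as a range.

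**Step 1: the plan's own figure.** Without the two proportions, 93 cannot be reproduced directly. I solved instead for pairs that give 93 per arm at 80% power under the plain pooled-variance formula, with p̄ = (p₁+p₂)/2:

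n = [1.96·√(2p̄(1−p̄)) + 0.8416·√(p₁(1−p₁)+p₂(1−p₂))]² / (p₁−p₂)²

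Pairs that fit include 5% vs 18.0%, 10% vs 25.6% and 20% vs 38.6%. For 10% vs 25.62%, p̄ = 0.1781 and n = (1.0605 + 0.4458)² / 0.1562² = 2.269 / 0.0244 ≈ 93.

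**Step 2: power after loss, plain formula.** With m = 93(1−d) evaluable per arm:

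power = Φ{ [|p₁−p₂|·√m − 1.96·√(2p̄(1−p̄))] / √(p₁(1−p₁)+p₂(1−p₂)) }

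For the same pair at d = 20%, m = 74.4 and power = Φ[(0.1562 × 8.626 − 1.0605) / 0.5297] = Φ(0.54) ≈ 70.6%. The pair hardly matters, because the expression is close to Φ[(1.96 + 0.84)·√(1−d) − 1.96]. At d = 20% that gives 70.7%.

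**Step 3: the same if 93 came from a continuity-corrected formula.** Here 93 = (n/4)·[1 + √(1 + 4/(n·|p₁−p₂|))]², where n is the plain result. The planned difference is then larger (5% vs 19.4% through 20% vs 39.8%), and an uncorrected test starts above 80%.

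| Assumed loss | Evaluable per arm | Power, plain formula | Power, 93 from corrected formula |
|---|---|---|---|
| 0% | 93 | 80.0% | 84–86% |
| 5% | 88.35 | 77.9% | 82–84% |
| 10% | 83.7 | 75.7% | 80–82% |
| 15% | 79.05 | 73.2% | 78–80% |
| 20% | 74.4 | 70.6% | 75–77% |
| 30% | 65.1 | 64.7% | 70–72% |

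**Step 4: sensitivity to sidedness.** A one-sided plain calculation gives 78.2%, 76.2%, 74.1%, 71.8% and 66.7% at 5%, 10%, 15%, 20% and 30% loss, so the pattern is the same.

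**The case against.** Three arguments on the other side have force.

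- **93 may already hold a margin.** The formula variant and the proportions rest on cited sources. With a continuity correction, a loss of about 10% still leaves 80%. This stands. A reader might infer that 80% power holds only if every randomised woman has an outcome, but the article does not support that; it is true only under the plain formula.
- **186 may count insertions.** The Sample size section words the two groups by insertion method received, and the Intervention section keeps the allocation in a sealed envelope until insertion. Several of the clinical withdrawal reasons arise before or around that moment. On this reading, many withdrawals would cost nothing. Against it, the Abstract speaks of this sample being randomised, and the eligibility section calls the withdrawn women randomised. The reading also leaves loss between insertion and the 40–60 day visit untouched. The ambiguity is real and is part of what needs settling.
- **Loss is possible, not certain.** A reader might infer that the withdrawals and the single visit rule out complete outcomes. They do not: no rate is given, and near-complete return is not excluded.

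Other stronger readings also lack support. Power of 75–76% with no loss under Fisher's exact test is doubly conditional: the article names no test beyond association tests, and that figure assumes the plain formula (with corrected pairs it is about 80–83%). Nothing in the article says that a non-significant result will be read as equal expulsion. Nor does it give a clinically important difference against which to call the detectable one too large. Finally, leaving out the two proportions, or a risk difference with its interval, is the condensing expected of an article and is not part of this point.

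**Conclusion.** The point holds as a moderate one. The article states 80% power for 186 women, makes no stated allowance for loss, describes the 186 as the sample to be randomised, and itself provides for withdrawal after randomisation and an outcome read at one later visit. The 80% is therefore not assured for the women analysed.

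The size depends on an assumed loss and on the unknown formula. Under the plain formula the shortfall is about 2 points of power at 5% loss, 4 at 10%, 9 at 20% and 15 at 30%. If a continuity correction was used, there is no shortfall at 10% loss and one of about 3–5 points at 20%. The effect is small when loss is small and the remedy is wording, so this does not rank as a must-fix.

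**What to change.** In the Sample size section, and in the Abstract where the claim is repeated, state whether 93 per arm means women randomised or women with a 40–60 day outcome. If it means women randomised, keep 186 and restate the power for the evaluable number under a named loss assumption: for example, about 71% at 20% loss under the plain formula. If a continuity correction was used, say so and give the matching figure.

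The cost is a sentence or two, with no change to recruitment or conduct. The downside is that the printed power becomes slightly less favourable. Holding 93 evaluable per arm instead would need 93/(1−d) randomised: 93/0.9 gives 104 per arm (208 in all) at 10% loss, and 93/0.8 gives 117 per arm (234 in all) at 20%. That is a larger trial, and this point does not require it.
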